#### Safety monitoring

All sites will report minor and serious adverse events that occur from baseline through to the 6-month follow-up. Two expert physiatrists will review reports outlining adverse events, if they arise, annually, to advise on trial continuation.

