### Quantitative component: randomized, controlled trial

#### Setting

The RCT will be conducted at three rehabilitation hospitals, GF Strong Rehabilitation Centre (Vancouver, Canada), Glenrose Rehabilitation Hospital (Edmonton, Canada), and Parkwood Institute (London, Canada). Participants will be recruited from each respective inpatient stroke rehabilitation units over a period of up to three years.

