#### Randomization

Participants will be randomized by the site coordinator after the baseline assessment at a one-to-one ratio to either the Exoskeleton group or Usual Care group using an online, third-party, permuted block randomization service (www.randomize.net, Interrand Inc., Ottawa, ON). As such, randomization will remain concealed until group allocation. Randomization will be stratified by site, to control for differences in standard of care (e.g., frequency and duration of physical therapy treatment, length of stay, rehabilitation and admission discharge timing, etc.). Participants will also be stratified by physical function, as baseline functioning is an independent predictor of outcomes such as community mobility and discharge destination [8, 26]. Specifically, participants will be stratified using their baseline Berg Balance Scale score at enrolment, as it has been shown to be correlated with improved walking ability after robot-assisted gait training [27]. A cut-off score of 12 will be used to stratify participants, based on a study [28] which identified a score of 12 at rehabilitation admission to be predictive of regaining unassisted walking after four weeks.

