#### Evaluations

All participants will be assessed at recruitment (baseline), at discharge or after 8 weeks of the intervention, and at 6 months by an assessor who is blind to group allocation. The exoskeleton intervention will be discontinued after 8 weeks, and standard physical therapy will be provided to all participants beyond 8 weeks for whom it is deemed appropriate by their care team.

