#### Sample size estimates

A total of 20 participants will be enrolled in each group (total same *n* = 40). This sample size was calculated using Stata Software (version 11, StataCorp, USA) and assumes a 2-point between-group difference in the Functional Ambulation Category at the end of the intervention [40], setting power at 80% and level of significance at 0.05 (2-sided). This calculation also assumes a standard deviation of 2.0 based on stroke inpatient FAC data from a study by Mehrholz et al. [30]. This between-group difference is realistic, given that participants are 2-person assist (score of 1 on the FAC) on enrolment, and it is expected that those in the Exoskeleton group will make greater improvements in walking ability (independent) compared to those receiving standard care (assistance or supervision required).

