### Trial status

Participant recruitment began on 5 May 2017 for GF Strong Rehabilitation Centre, on 7 December 2017 for Glenrose Rehabilitation Hospital, and on 8 August 2018 for Parkwood Institute. Participant recruitment is ongoing and projected to be completed by December 31, 2020.

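### The adverse event review that advises on trial continuation is fixed at once a year, a long interval for serious events when device use lasts at most 8 weeks

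*Protocol article*

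**What the plan says.** The Safety monitoring section of the protocol article has two sentences. The first covers reporting: "All sites will report minor and serious adverse events that occur from baseline through to the 6-month follow-up". The second covers review: "Two expert physiatrists will review reports outlining adverse events, if they arise, annually, to advise on trial continuation". It thus fixes who reviews, how often and for what purpose, and it does not separate serious events from minor ones.

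Other sections give the exposure and its pace:

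- Evaluations: "The exoskeleton intervention will be discontinued after 8 weeks".
- Sample size estimates: "A total of 20 participants will be enrolled in each group". Under Randomization, allocation is "at a one-to-one ratio to either the Exoskeleton group or Usual Care group".
- Setting: recruitment runs "over a period of up to three years".
- Trial status: "Participant recruitment began on 5 May 2017 for GF Strong Rehabilitation Centre", with the other two sites following on 7 December 2017 and 8 August 2018. "Participant recruitment is ongoing and projected to be completed by December 31, 2020".
- Table 2 (Secondary outcomes) lists an adverse events screen that is kept up through the intervention period and repeated at six months.

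**The concern.** The stated purpose of the review is to advise whether the trial should go on. For a serious event the value of that advice depends on how soon it comes, because it bears on people who have not yet started on the device. With a yearly interval, a serious event shortly after one review would wait almost a year for the next. Everyone on the device when it happened would have finished by then, and others would have started in the meantime.

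The setting makes serious events worth planning for. Participants need maximal help from one or two people to walk (Participants), and the device leaves balance to the user (Exoskeleton device). At stake is the number of people who begin device training before the reviewers give advice on continuation.

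**Working it through.** The article states no figure for exposure between reviews, so there is none to reproduce. The check is how many device participants would start between two annual reviews.

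**Inputs from the article**
- Review interval: 12 months (Safety monitoring).
- Longest device exposure: 8 weeks (Evaluations).
- Device group: 20 of 40 (Sample size estimates, Randomization).
- Recruitment period: 3 years (Setting), or 5 May 2017 to 31 December 2020 (Trial status), which is 1336 days; 1336 / 365.25 = 3.66 years. Both are used.

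**Assumption.** The article gives no enrolment by date. Even accrual is assumed first, then accrual in proportion to the sites open.

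**Step 1: interval against exposure.** 365.25 / 56 = 6.5, so a year holds about 6.5 consecutive intervention periods. This describes the mismatch but is not a criterion of timeliness; the count of people exposed matters more.

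**Step 2: worst case, an event just after a review (lag 12 months).** Device participants starting = 20 / recruitment years.
- 3 years: 20 / 3 = 6.7, which is 33% of 20.
- 3.66 years: 20 / 3.66 = 5.5, which is 27% of 20.

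**Step 3: average case.** If the event is equally likely at any time between reviews, the mean lag is 6 months, and the counts halve: 6.7 / 2 = 3.3 and 5.5 / 2 = 2.7, or about 3 participants.

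**Step 4: those who start and also complete all 8 weeks within the year.** Multiply the counts in Step 2 by 1 − 8/52.18 = 0.847.
- 3 years: 6.67 × 0.847 = 5.6 (28%).
- 3.66 years: 5.47 × 0.847 = 4.6 (23%).

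**Step 5: staggered site openings.** To 31 December 2020 the sites contribute 3.66 + 3.07 + 2.40 = 9.12 site-years (from unrounded values). With an equal rate per open site, the share in a period is its site-years / 9.12.

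| Period from 5 May 2017 | Site-years | Share | Device participants |
|---|---|---|---|
| Year 1 | 1.41 | 15% | 3.1 |
| Year 2 | 2.74 | 30% | 6.0 |
| Year 3 | 3.01 | 33% | 6.6 |
| Remainder | 1.97 | 22% | 4.3 |

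The first year is well below the even-accrual figure. Years 2 and 3 lie within or close to its range.

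**Step 6: what a late review can still affect.** If reviews fall on the anniversaries of the first site's opening, advice at the end of year 1 still has 67% of device enrolment ahead of it (even accrual, 3 years), 73% (even accrual, 3.66 years) or 85% (staggered). At the end of year 2 the figures are 33%, 45% and 55%.

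**The case against.** The strongest reply is that this is a condensed article. Expedited handling of serious events is commonly left to the full protocol, which is not shown, and its absence here is no fault. A reader might infer that serious events go unexamined for up to a year. The documents do not support that: Table 2 provides screening throughout the intervention, sites report minor and serious events through to six months, and the article is silent on how those reports are handled between annual reviews. This part of the objection stands, and it confines the point to the interval that the article does state.

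A reader might also infer that the review cannot act in time to protect the participants it concerns. That is too strong. A review that happens to follow soon after an event could still help people then on the device, and any review can help those not yet enrolled; Step 6 shows that a substantial share often remains. Day-to-day protection lies with the treating staff: therapists control the device settings and training is progressed as tolerated. The Background section also reports early evidence of safe use in stroke.

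Finally, 27% to 33% is a worst case on assumed accrual, and the first-year figure is nearer 15%. That stands too. An annual cumulative review is a reasonable layer of oversight in itself.

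The objection does not remove the stated rule. The section sets one interval for all events and ties it to advice on continuation. Reporting to other bodies would not change when these two reviewers give that advice.

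**Conclusion.** The point holds in a limited form. The yearly interval fits its stated purpose poorly where serious events are concerned. As written, continuation advice could lag by up to 12 months, during which about 3 further device participants would start on average and 5 to 7 of 20 in the worst case. These counts assume even accrual over 3 or 3.66 years and an event time unrelated to the review date; with staged site openings the first-year count is about 3 over the whole year.

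The documents do not support a conclusion that safety monitoring is absent or that expedited reporting is lacking. Nor is there a contradiction or a wrong figure, and the efficacy analysis is unaffected. This is a worthwhile, low-cost improvement to trial oversight.

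**What to change.** Amend the Safety monitoring section so that the same two physiatrists review each serious adverse event within a fixed short period after the site reports it, and advise on continuation at that time. Keep the annual meeting for cumulative review of all events, minor and serious. If the full protocol already provides for such a review, align this section with it.

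The change takes about one sentence and needs no new reviewers. It concerns oversight only and sets no treatment or clinical rule. The cost is a few unscheduled reviews, likely to be manageable in a trial of 40. As the article describes recruitment as ongoing, the change could still benefit later participants.

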#### Sample size estimates

A total of 20 participants will be enrolled in each group (total same *n* = 40). This sample size was calculated using Stata Software (version 11, StataCorp, USA) and assumes a 2-point between-group difference in the Functional Ambulation Category at the end of the intervention [40], setting power at 80% and level of significance at 0.05 (2-sided). This calculation also assumes a standard deviation of 2.0 based on stroke inpatient FAC data from a study by Mehrholz et al. [30]. This between-group difference is realistic, given that participants are 2-person assist (score of 1 on the FAC) on enrolment, and it is expected that those in the Exoskeleton group will make greater improvements in walking ability (independent) compared to those receiving standard care (assistance or supervision required).

#### Statistical analyses

Descriptive statistics will be used to summarize data. An analysis of covariance (ANCOVA) will be performed to detect post-intervention differences between groups for the primary and secondary measures, using the respective baseline score as the covariate [41]. The significance level will be set at 0.05, and all statistical tests will be two-tailed. Participant data will be analyzed on an intention-to-treat basis, and any missing data will be assessed and analyzed as appropriate using multiple imputation [42]. For measures without a baseline score (i.e., 5-Metre Walk Test, 6-Minute Walk Test), an analysis of variance (ANOVA) will be employed. Confidence intervals (95% CIs) will be reported, where applicable.

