#### Participants

Consecutive patients with subacute stroke admitted at each rehabilitation hospital will be identified by their treating physiatrists and therapists to be screened for eligibility by a member of the research team. Individuals will be included if they: 1) are within 3 months of stroke onset (ischemic infarct or intracerebral hemorrhage); 2) have one-sided hemiparesis; 3) are 19 years of age or older; 4) are able to understand and follow directions in English; 5) are able to communicate (verbal or physical yes/no indication); 6) are cleared to participate in physical therapy; and 7) require significant assistance (maximal assistance from one or two people) to walk. Individuals will be excluded from the study if they have: 1) a significant musculoskeletal or other neurological condition; 2) cardiovascular contraindications to exercise; 3) co-morbidities that would preclude activity; 4) or pain which is intolerably worsened with exercise. Individuals will also be excluded if they have any contraindications to using the robotic exoskeleton (pregnant, height/weight restrictions). The site coordinator at each hospital with obtain informed consent from potential trial participants.

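### The primary ANCOVA adjusts only for baseline FAC, which eligibility holds near its floor, and leaves out the stratification factors (site and Berg Balance Scale), so precision is lost

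*Protocol article*

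**What the plan says.** All references are to the protocol article.

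- **Statistical analyses.** Primary and secondary measures are compared after the intervention by ANCOVA, "using the respective baseline score as the covariate". Measures with no baseline value get an ANOVA. No other covariate is named.
- **Primary outcome.** FAC runs from 1 (two helpers needed) to 6 (independent on uneven ground and stairs).
- **Sample size estimates.** The text says that "participants are 2-person assist (score of 1 on the FAC) on enrolment".
- **Participants.** The operative criterion is a little looser. Patients must "require significant assistance (maximal assistance from one or two people) to walk".
- **Randomization.** "Randomization will be stratified by site, to control for differences in standard of care". It is also stratified by Berg score with a cut at 12, on the ground that "baseline functioning is an independent predictor of outcomes such as community mobility and discharge destination". The section adds that the Berg score is correlated with walking gains after robot-assisted training and that a score of 12 predicted unassisted walking at four weeks.

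**The concern.** A baseline covariate improves precision only if it varies between participants and predicts the outcome. Baseline FAC can hardly vary in this trial, because the entry criterion selects on what it measures. The two variables that the article gives reasons to expect to be prognostic are balanced by design and then left out of the model.

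Stratifying on a prognostic factor removes part of the between-arm chance variation. A model without that factor still counts the variation as residual error. The reported standard error then exceeds the true one, the test rejects less often than 5% under the null, and the interval is wider than it need be. With 40 participants, precision is the scarce resource, and both omitted variables are already available for everyone at baseline.

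**Working it through.** **1. The plan's own power.** Inputs from Sample size estimates: the plan "assumes a 2-point between-group difference in the Functional Ambulation Category" and "assumes a standard deviation of 2.0", with 80% power, two-sided 0.05 and 20 per group.

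- Normal approximation: n = 2(1.96 + 0.842)² × 2.0² / 2² = 15.7, so 16 per group. The noncentral t gives 17.
- The stated 20 per group is not reproduced from these inputs alone. An unstated dropout allowance would give it (16/0.80 = 20 or 17/0.85 = 20). The present point does not depend on this.
- At 20 per group the standard error is 2.0 × √(2/20) = 0.632. Noncentrality is 2/0.632 = 3.16, and with 38 degrees of freedom power is 86.9%. The 95% CI half-width is 2.024 × 0.632 = 1.28 points.

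**2. What baseline FAC contributes.** If everyone scores 1, the covariate is constant, cannot be separated from the intercept, and the ANCOVA is a two-sample t test. If instead 30% score one category higher (an assumption, correlated with Berg), simulated mean CI width changes by no more than about 0.04 points on about 2.55.

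**3. What site and Berg could contribute.** Let R² be the share of outcome variance explained by Berg. The article gives no value, so 10%, 25% and 40% are assumed. Residual SD is 2.0 × √(1 − R²). Treatment, site (2 df) and continuous Berg (1 df) leave 35 degrees of freedom, with critical value 2.030.

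| Assumed R² | Residual SD | Half-width | Against 1.28 | Power at 2 points |
|---|---|---|---|---|
| 0 | 2.00 | 1.28 | about 0.3% wider | 86.7% |
| 10% | 1.90 | 1.22 | 5% narrower | 90.0% |
| 25% | 1.73 | 1.11 | 13% narrower | 94.4% |
| 40% | 1.55 | 0.99 | 22% narrower | 97.8% |

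**4. Simulation.** This allows for incomplete blocks and residual imbalance. Settings: 40 participants, three sites by two Berg strata, SD 2.0, and permuted blocks of 4 (assumed; the article gives no block size).

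| Assumed Berg R² | Type I error as written | CI narrowing, continuous Berg + site | CI narrowing, Berg cut at 12 + site | Power at 2 points, continuous Berg + site |
|---|---|---|---|---|
| 10% | about 4.0% | 4% | 3% | about 90% |
| 25% | about 3.3% | 13% | 8% | about 93% |
| 40% | about 2.5% | 22% | 13% | about 97% |

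As written, power at 2 points is about 87–89% across these rows. Separate runs differ by about a percentage point; one gave 3.4% type I error at R² = 40%. With site and Berg in the model, type I error returns to about 5%. At R² = 0 the adjustment widens the interval by about 1%.

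**5. Why the cut score gains less.** If the cut falls near the median of a normal score (assumed), it keeps 2/π = 0.637 of the explained variance: 6.4%, 15.9% and 25.5%. Then √(1 − 0.064) = 0.968, √(1 − 0.159) = 0.917 and √(1 − 0.255) = 0.863. Multiplying by 2.030/2.024 gives intervals about 3%, 8% and 13% narrower, as simulated.

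**The case against.** The strongest reply is that nothing here is invalid. Randomization keeps the estimate unbiased, type I error stays at or below 5%, and power at the planned difference is about 87% against a target of 80%. That stands. A reader might infer that the trial is underpowered or its primary result unreliable; the article's own inputs do not support this. Power drops to about 64% at a 1.5-point difference, but that is not the planned effect.

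A reader might also infer that the ANCOVA necessarily reduces to a t test. That rests on one sentence in the sample size rationale. The eligibility criterion admits one-person maximal assistance, so some variation in baseline FAC is possible, and dropping it outright would go too far.

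Nor is it right that stratifying by site does nothing for the analysis. It still limits chance imbalance in the treatment estimate; only the standard error fails to credit it.

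Part of the gain is not about matching the analysis to the randomization. The stratifier is Berg cut at 12, and the larger figures come from using the full score. The R² values are assumptions: the article says Berg is predictive but gives no share of variance, and at 10% the gain is small.

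Finally, a full analysis plan may add the stratifiers. The article is not silent, however: it states the model and names its covariate.

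**Conclusion.** The point holds as one of efficiency and should be fixed; it does not threaten validity. The stated covariate adjusts for almost nothing, and the model omits the two factors on which the design stratifies. The direction follows from the text, provided those factors predict post-intervention FAC, as the article argues for baseline function. The size does not follow from the text: a CI narrower by about 4% to 22% with continuous Berg, or 3% to 13% with the cut score, rests on an assumed R² of 10% to 40%, blocks of 4 and SD 2.0.

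The power margin also assumes full follow-up. As written, power at 2 points is 81% with 17 completers per arm and 78% with 16. If site and Berg explain 20% of variance, the adjusted model has about 88% and 86%. The Discussion anticipates some withdrawals from Usual Care, so the recovered precision could matter.

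**What to change.** Before unblinding, prespecify the primary model as post-intervention FAC on treatment, site and baseline Berg score as a continuous variable, keeping baseline FAC only if it varies. For the secondary outcomes, add site and Berg alongside each measure's own baseline score (for the Berg outcome itself, only site is new), and add both to the ANOVAs for measures with no baseline. Include site and Berg in the imputation model.

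The cost is a sentence or two in the analysis section and about 3 degrees of freedom. No new data are needed: Berg is already in the baseline assessment, and site is known. If neither factor predicts outcome, the interval widens by only about 1%. Choosing the covariates after seeing results by arm would forfeit the benefit.

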### Qualitative component: interpretive description

This qualitative descriptive study will be conducted concurrently with the randomized controlled trial to determine the acceptability of the exoskeleton device for stroke rehabilitation from the perspective of patients with stroke and their physical therapists. The qualitative description methodology is useful when a straight description of phenomena is required, without the need for developing theory [43]. It is a rigorous methodology that provides a comprehensive summary of experiences and perceptions that is often used in health sciences research [43]. The qualitative design was informed by the COREQ (Consolidated criteria for reporting qualitative research) checklist [44], which will be used to report the qualitative findings.

#### Approach

This study will be based in a postpositivist paradigm [45], assuming that exoskeleton users will have individual yet relatively patterned experiences and perceptions of the device. According to this paradigm, conclusions that are drawn regarding the acceptability of using a powered robotic exoskeleton can be generalized to other stroke rehabilitation sites regardless of the social contexts of the researcher and participants of this study.

#### Participants

Participants randomized to the Exoskeleton group in the quantitative RCT will be recruited from all sites to participate in qualitative interviews. All participants who undergo at least five training sessions in the exoskeleton will be invited to participate, provided they are able to communicate fully (English proficiency, non-severe aphasia). It is expected that 10–15 participants with stroke will be thus be eligible and interviewed, during which time data sufficiency will be reached and identified themes would not need to be adjusted by further data collected [46, 47].

All physical therapists who have been fully trained to use the exoskeleton device and who provide the intervention for the RCT will be invited to participate in qualitative interviews. Five to 10 physical therapists are expected to be eligible and participate.

